**Abstract**

**Background**

There is a growing global need for scalable approaches to training and supervising primary care workers (PCWs) to deliver mental health services. Over the past decade, the World Health Organization Mental Health Gap Action Programme Intervention Guide (mhGAP-IG) and associated training and implementation guidance have been disseminated to more than 100 countries. On the basis of the opportunities provided by mobile technology, an updated electronic Mental Health Gap Action Programme Intervention Guide (e-mhGAP-IG) is now being developed along with a clinical dashboard and guidance for the use of mobile technology in supervision.

**Objective**

This study aims to assess the feasibility, acceptability, adoption, and other implementation parameters of the e-mhGAP-IG for diagnosis and management of depression in 2 lower-middle-income countries (Nepal and Nigeria) and to conduct a feasibility cluster randomized controlled trial (cRCT) to evaluate trial procedures for a subsequent fully powered trial comparing the clinical effectiveness and cost-effectiveness of the e-mhGAP-IG and remote supervision with standard mhGAP-IG implementation.

**Methods**

A feasibility cRCT will be conducted in Nepal and Nigeria to evaluate the feasibility of the e-mhGAP-IG for use in depression diagnosis and treatment. In each country, an estimated 20 primary health clinics (PHCs) in Nepal and 6 PHCs in Nigeria will be randomized to have their staff trained in e-mhGAP-IG or the paper version of mhGAP-IG v2.0. The PHC will be the unit of clustering. All PCWs within a facility will receive the same training (e-mhGAP-IG vs paper mhGAP-IG). Approximately 2-5 PCWs, depending on staffing, will be recruited per clinic (estimated 20 health workers per arm in Nepal and 15 per arm in Nigeria). The primary outcomes of interest will be the feasibility and acceptability of training, supervision, and care delivery using the e-mhGAP-IG. Secondary implementation outcomes include the adoption of the e-mhGAP-IG and feasibility of trial procedures. The secondary intervention outcome—and the primary outcome for a subsequent fully powered trial—will be the accurate identification of depression by PCWs. Detection rates before and after training will be compared in each arm.

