
### Study Design

A feasibility cluster randomized controlled trial (cRCT) will be conducted to evaluate and compare the implementation outcomes [32] and clinical outcomes of the adapted e-mhGAP-IG v2.0 and the paper version of the mhGAP-IG v2.0. A total of 10 PHCs in each country (Nepal and Nigeria) will be randomized to training, supervision, and care delivery using the paper mhGAP-IG (control arm) or the e-mhGAP-IG (experimental arm), and outcomes of PCWs and patients will be collected over a 9-month period (Figure 1). Data collected through the feasibility study will be used to further refine the intervention (eg, acceptability and feasibility for randomization and recruitment) and power a subsequent cRCT.

Figure 1.

[figure not shown]

Feasibility study patient and provider data collection procedure. mhGAP: Mental Health Gap Action Programme;  $P_0$ : patient pre training assessment;  $P_1$ : patient baseline health care appointment assessment;  $P_2$ : patient 3 months post baseline health care appointment; PCW: primary care worker;  $PCW_0$ : primary care worker baseline assessment;  $PCW_1$ : primary care worker immediate post training assessment;  $PCW_2$ : primary care worker 3 months post training assessment;  $PCW_3$ : primary care worker 8 months post training assessment;  $S_0$ : Supervisor baseline assessment;  $S_1$ : Supervisor 8 months post training assessment.

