## Statistical Power and Sample Size Calculation

The study will take place in 1 government administrative region in Nepal and 4 in Nigeria. We will identify approximately 20 PHCs in Nepal and 6 in Nigeria. In each country, half of the PHCs will be randomly allocated to either the e-version or the paper version of the mhGAP-IG. As the clinics vary in size, we will assess at least two staff members in each clinic, with an estimated 2-5 health workers per facility and an overall enrollment of 40 PCWs in Nepal and 30 PCWs in Nigeria. Regarding patient numbers, on the basis of the sample size for the study by Sangha et al [34] on smartphone app for improving cognition to improve case detection, we will conduct within-arm comparison detection rates if at least 40 patients screen positive on the Patient Health Questionnaire (PHQ-9) in the research assistant interview in the 1-month pretraining period and in the first month of the posttraining patient enrollment period, which begins after 3 months of intensive supervision. This will allow us to detect a within-arm increase in the clinical case identification rate of 43% for the e-mhGAP-IG after the implementation of the e-version with 90% power at the 5% level of significance, assuming an intraclass correlation coefficient of 0.02. For example, with a 10% detection rate pretraining, 2 patients would receive a health worker depression diagnosis out of 20 patients screening positive. After training, the detection rate would increase to 53%, which equates to 11 patients diagnosed by a health worker out of 20 patients screening positive.

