#### PCW and Patient Outcome Analysis

The primary outcome will be the accuracy of the depression diagnosis. The research team will identify a patient as screening positive based on the PHQ-9 result immediately before or after the patient sees the PCW. *Screening positive* will be defined as scoring  $\geq 10$  on the PHQ-9. The research team will also assess sensitivity to change, for change in both the PHQ-9 and WHODAS 2.0 scores from baseline and 3 months after initiation of treatment. *Positive diagnosis* will be defined as a clinical diagnosis of depression documented by the health worker in the clinical notes. *Accurate detection* will be defined as PHQ-9  $\geq 10$  and a health worker depression clinical diagnosis. We will also report findings in terms of the sensitivity and specificity of health worker diagnoses. *Sensitivity* will be defined as the proportion of health worker–diagnosed patients who had PHQ-9 above the cutoff, out of all patients who scored above the PHQ-9 cutoff. *Specificity* will be defined as the proportion of patients who did not receive a health worker depression diagnosis and scored below the PHQ-9 cutoff, out of all patients scoring below the PHQ-9 cutoff.

Features of the cRCT design will be accommodated in all analyses, and an intention-to-treat approach will be used. The principles of analysis will be (1) the PHC-level accuracy outcome is binomial (ie, number of accurate diagnoses out of all diagnoses based on patient-level data), and therefore, a generalized linear mixed model will be used (specifically, a log-binomial regression to obtain probability ratios); (2) accuracy is a cumulative measure, and therefore, there are no repeated measures over time; and (3) missing data can occur at either the health worker or patient level.

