Differences in detection rates will be assessed using patient outcome data at 3 months after enrollment, only in depression cases identified in each arm (ie, scoring  $\geq 10$  on the PHQ-9), and the health worker clinical diagnosis. A 3-level hierarchical model will be used when all time points will be included as repeated measures in the model to improve power and take into account clustering of the observation at patient and PHC levels. The 3-level linear mixed model will be used to estimate a 95% CI for the comparison of clinical diagnosis and PHQ-9 screening positive rates (as well as a subanalysis with PHQ-9 plus WHODAS 2.0 criteria) within electronic and paper mhGAP-IG versions. Secondary outcomes (eg, knowledge and attitudes) will be assessed within each arm with a similar methodology for the primary outcomes, using generalized linear mixed models depending on the type of outcome (normal, binary, and count). Clinical feasibility will also be triangulated using penetration and costing data.

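### Every detection contrast the protocol spells out is within arm, and the randomised e-version versus paper contrast it promises is left undefined

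*Protocol*

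**What the plan says.** The Study Design section of the protocol states that the trial will evaluate and compare the implementation outcomes and "clinical outcomes of the adapted e-mhGAP-IG v2.0 and the paper version of the mhGAP-IG v2.0", and that its data will help power a later cluster trial. The Health Economic Analysis section sets the electronic tool against the paper one, using detection rates from the study.

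The contrasts that are spelled out are different:

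- Abstract, Methods: "Detection rates before and after training will be compared in each arm".
- Statistical Power and Sample Size Calculation: "we will conduct within-arm comparison detection rates if at least 40 patients screen positive on the Patient Health Questionnaire (PHQ-9"; then "This will allow us to detect a within-arm increase in the clinical case identification rate of 43% for the e-mhGAP-IG", "with 90% power at the 5% level of significance, assuming an intraclass correlation coefficient of 0.02".
- PCW and Patient Outcome Analysis, last paragraph: a three-level model gives a 95% CI within the electronic and within the paper version, with all time points entered as repeated measures. Secondary outcomes such as knowledge and attitudes "will be assessed within each arm with a similar methodology for the primary outcomes".

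The paragraph before that one, in the same section, promises intention-to-treat and a log-binomial mixed model giving probability ratios. It states that accuracy is cumulative and so is not measured repeatedly over time. It does not say which groups form the ratio.

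The outcome hierarchy also varies. The abstract says "The primary outcomes of interest will be the feasibility and acceptability of training, supervision, and care delivery using the e-mhGAP-IG" and makes detection the secondary intervention outcome. PCW and Patient Outcome Analysis says "The primary outcome will be the accuracy of the depression diagnosis", and Implementation Outcome Analysis likewise calls the change in detection rate primary.

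**The concern.** Clinics are randomised between guides, so the comparison that randomisation protects is electronic versus paper. A before-after change within one arm is not that comparison. Both arms receive mhGAP training and remote supervision, and both have the paper guide available (Table 1). Post-training enrolment starts 3 months after training, and COVID-19 delays are noted under Results. A rise in either arm therefore combines the guide with training, supervision, the presence of research staff and calendar time.

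Two separate within-arm tests at the 5% level also invite an informal comparison of their P values. One arm can cross the threshold and the other miss it when the guides are equally good. The later trial needs a between-arm estimate and its precision, and none of the spelled-out contrasts supplies these.

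**Working it through.** **1. The plan's own figure.** Inputs from Statistical Power and Sample Size Calculation: detection 10% (2 of 20) before training and 53% (11 of 20) after, 5% level, ICC 0.02. Two-sided testing is assumed, as sidedness is not stated. With unpooled variance:

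SE = sqrt[(0.10×0.90 + 0.53×0.47)/20] = 0.130; 0.43/0.130 = 3.30; power = Φ(3.30 − 1.96) = 91.0%.

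With 2 positives per clinic (20 over 10 clinics, as in one Nepal arm) the design effect is 1 + (2 − 1)×0.02 = 1.02 and power is 90.5%. The stated 90% is thus reproduced, as a before-after comparison in one arm. A pooled-variance formula gives 86.2% without a design effect.

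**2. Chance of a split when the guides are equally good.** With the same true rise in both arms and independent arms, P(exactly one arm significant) = 2 × power × (1 − power). At the stated 90% power this is 2×0.90×0.10 = 18%. Power below comes from exact enumeration of the uncorrected chi-square test, without clustering. The protocol does not say whether its 40 positives are per arm and per period, and its worked example uses 20, so both are shown.

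| Positives per arm per period | True rise in both arms | Power in each arm | P(exactly one significant) |
|---|---|---|---|
| 20 | 10% to 53% (planned) | 88% | 21% |
| 20 | 10% to 40% | 62% | 47% |
| 20 | 10% to 35% | 49% | 50% |
| 40 | 10% to 53% (planned) | 99% | 1.3% |
| 40 | 10% to 40% | 90% | 18% |
| 40 | 10% to 35% | 79% | 33% |

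First row: 2×0.883×0.117 = 0.21. The rises to 40% and 35% are assumed; only 53% stands in the protocol.

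**3. What a between-arm estimate would deliver.** The Participants section anticipates 200 screens per arm per country per month, so 600 per arm over the three post-training months. Assume that the prevalences under Settings (16.8% in Nepal primary care, 5.5% in Nigeria) equal the screen-positive rates, and that detection is 40%.

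- Nepal: 600×0.168 ≈ 101 positives per arm, about 10 per clinic over 10 clinics; design effect 1.18. Half-width = 1.96×sqrt(2×0.4×0.6/101×1.18) = 0.147.
- Nigeria: 600×0.055 = 33 per arm, 11 per clinic over 3 clinics; design effect 1 + 10×0.02 = 1.20. Half-width = 1.96×sqrt(2×0.4×0.6/33×1.20) = 0.259.

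These use normal quantiles. With t on 18 and 4 degrees of freedom (clinics minus two) they become 0.147×2.10/1.96 = 0.158 and 0.259×2.78/1.96 = 0.367. The clinic counts are the 20 and 6 given under Participants; Study Design gives 10 per country.

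A difference in change is wider than a post-training difference. At 20 positives per arm per period and 53% after training, without a design effect, the half-widths are 1.96×sqrt(2×0.53×0.47/20) = 0.31 for the post-training difference and 1.96×sqrt[2×(0.53×0.47 + 0.10×0.90)/20] = 0.36 for the difference in change.

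**4. The two analysis paragraphs side by side.** One treats accuracy as cumulative, not repeated over time, and estimates a ratio. A ratio without a time dimension can hardly be before-after, so it suggests arm against arm. The next paragraph enters all time points as repeated measures and reports intervals within each version. They cannot both describe the same detection analysis, and neither names electronic versus paper as its estimate.

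**The case against.** A reader might infer that detection is compared only before-after, that the randomised contrast is never estimated, and that randomisation adds nothing. The document does not support that. The intention-to-treat log-binomial model points to a between-arm ratio, Study Design promises a comparison of the two versions, and the economic model sets one tool against the other. Randomisation also has its own purpose here, since its acceptability and feasibility are among the things being tested.

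The feasibility purpose counts as well. The stated objective for detection is to describe it, the progression criteria do not use it, and a feasibility trial need not power or test a between-arm effect. No section says that significance in one arm and not the other will be read as superiority, so that harm is a risk and not a stated plan. Model terms and baseline adjustment may sit in an SAP that was not available. The word primary in the outcome-analysis section may mean primary within that class of outcomes.

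These points remove the strong reading. They do not remove the defect: the protocol itself fixes within-arm contrasts, including a 5%-level test that goes beyond description; it leaves the groups of its one apparently between-arm model unnamed; and its two detection paragraphs disagree.

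**Conclusion.** The point holds in this limited form: the within-arm contrasts are explicit, while the between-arm contrast is promised but undefined, with conflicting models. The chance of a misleading split between equally good guides is 21% at the planned effect with 20 positives per arm per period and nearly one in two for a smaller shared rise. It is negligible (1.3%) at the planned effect with 40, but 18-33% for the smaller rises. These figures assume independent arms, two-sided tests and no clustering.

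The between-arm half-widths, about 15 points in Nepal and 26 in Nigeria, rest on the assumed screen-positive rates, 40% detection and ICC 0.02. The few-clinic correction matters most in Nigeria. At that precision the contrast is useful as an estimate and not as a test. The primary/secondary label for detection is a separate inconsistency to correct alongside.

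**What to change.** In the abstract, the sample-size section and PCW and Patient Outcome Analysis:

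- Name electronic versus paper as the detection contrast, from one model with arm, period, arm by period and country that respects clustering by clinic. Reconcile the log-binomial paragraph with the three-level paragraph so that one analysis is described.
- Report the between-arm ratio and difference in detection with 95% CIs, using a small-sample correction for few clinics, as estimates without a significance claim.
- Show within-arm changes descriptively, and do not infer a difference between guides from separate within-arm tests.
- Analyse health worker knowledge, attitude and competence scores between arms, adjusted for the baseline score.
- Call detection the secondary intervention outcome throughout, including in Implementation Outcome Analysis.

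The cost is analysis wording; no data collection changes. The drawback is a wide between-arm interval, which is a fair account of what a feasibility trial can show.

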**Results**

To date, qualitative formative work has been conducted at both sites to prepare for the pilot feasibility cRCT, and the e-mhGAP-IG and remote supervision guidelines have been developed.

**Conclusions**

The incorporation of mobile digital technology has the potential to improve the scalability of mental health services in primary care and enhance the quality and accuracy of care.

Trial Registration

ClinicalTrials.gov [NCT04522453](https://clinicaltrials.gov/ct2/show/NCT04522453); <https://clinicaltrials.gov/ct2/show/NCT04522453>.

International Registered Report Identifier (IRRID)

PRR1-10.2196/24115

**Keywords:** mental health, community mental health, digital technology, primary health care, intervention, eHealth, mHealth, LMIC, remote supervision, training, mobile phone

## Introduction

### Background

Mental illnesses are common, affecting 1 in every 3 people during their lifetime [1]. Globally, mental illnesses are the leading contributor of years lived with a disability [2]. Despite the prevalence and impact of mental illness, a large difference between true and treated prevalence rates of mental disorders, also known as the mental health treatment gap, exists. It is estimated that more than 80% of people with severe mental illness in low- and middle-income countries (LMICs) receive no treatment [3]. Only 16.5% of people with depression living in LMICs have access to minimally adequate treatment [4]. The consequences of this treatment gap include symptom persistence and deterioration, social exclusion, and long-term disability of people who could be economically productive and socially included. Globally, there is growing recognition of the importance of mental health, as evidenced by its incorporation in the United Nations 2030 Agenda for Sustainable Development and extension of the World Health Organization (WHO) Comprehensive Mental Health Action Plan to 2030 by the World Health Assembly [5].

The limited number of mental health specialists and the concentration of care in hospital settings in urban rather than rural areas limit the availability and accessibility of care [6]. Low treatment rates in LMICs are related to poor demand and supply-side forces. High levels of stigma associated with mental illness manifest in low rates of help seeking among those who would benefit from care [7-10]. The WHO recommends a task-shifting approach to strengthen the generalist workforce and improve access to health care, including mental health care [11]. However, this method requires the availability of evidence-based tools and appropriate training, supervision, and support.

In recent years, there has been an exponential rise in global access to mobile technologies in LMICs. In 2012, there were 287 million unique mobile phone subscribers across sub-Saharan Africa, covering 32% of the population [12]. Moreover, 6 years later, that number rose to 465 million, representing 44% of the population. In Nepal, the number of mobile contracts (27.85 million) surpasses the total population (26.49 million) [13]. The increased application of mobile technology to the health care arena, known as mobile health (mHealth), aims to provide a powerful platform to improve the quality of interventions using a task-shifting approach and reduce the treatment gap. mHealth refers to the use of mobile technology in health interventions and service provision [14]. In a recent WHO survey, 87% of the responding countries reported at least one government-sponsored mHealth program in their country [14]. However, only 14% of countries reported an evaluation of these programs, raising concerns about insufficient evidence of impact.

A systematic review of smartphone use in clinical decision-making by health care professionals identified 7 randomized controlled trials conducted in high-income settings, which demonstrated improved knowledge, diagnosis, treatment decisions, and documentation using mHealth technology [15]. Studies on mHealth tools in LMICs have yielded mixed results [16]. Qualitative data, however, suggest that the intervention facilitated task shifting and improved health workers' morale.

In 2010, the WHO launched the Mental Health Gap Action Programme Intervention Guide (mhGAP-IG) [17], an evidence-based assessment and management guide for mental, neurological, and substance use conditions designed for use by primary and community health staff in LMICs [18].

The first edition of the mhGAP-IG (v1.0) has been implemented in over 100 countries. An updated version (v2.0) was launched in 2016, with new sections and updated evidence-based guidance [17], along with a first version of a smartphone app available for both Android and iOS devices in 2017. The mhGAP-IG v2.0 consists of 8 modules addressing priority conditions (ie, depression, psychoses, epilepsy, child and adolescent mental and behavioral disorders, dementia, disorders due to substance use, self-harm or suicide, and other significant mental health complaints that impair daily functioning or lead to help seeking). It provides an overview of common presentations for each condition, followed by detailed guidance for assessment, management (including referral to specialist care), and follow-up.

The Emilia (E-mhGAP Intervention Guide in Low- and Middle-Income Countries: Proof-of-Concept for Impact and Acceptability) project seeks to readdress the treatment gap by developing a potentially practical way for primary care workers (PCWs) to diagnose and treat people with mental illness according to evidence-based guidelines.

### Aims and Objectives

Emilia aims to test the feasibility of an updated electronic Mental Health Gap Action Programme Intervention Guide (e-mhGAP-IG) and trial procedures for the future conduct of a large-scale trial, which would evaluate differences in depression detection between facilities using the e-mhGAP-IG versus the paper mhGAP-IG. The objectives of this feasibility study, in preparation for a future trial, include the following:

1. To evaluate the feasibility and overall implementability of primary care mental health services using the e-mhGAP-IG for training, supervision, and delivery of care (primary objective).
2. To determine recruitment and retention rates of PCWs and patients.
3. To establish the acceptability and feasibility of assessing PCW and patient outcomes.
4. To assess ethics and safety procedures using adverse event reporting.
5. To describe depression detection rates in primary health clinics (PHCs).
6. To describe depression treatment outcomes in PHCs.

